
**Fig. 1 Fig1:**
[figure not shown]
Postoperative dressing of the abdomen until discharge (picture with patient consent)

Any deviation from the planned surgery including conversion from iRARC to ORC will be at the operating surgeon’s discretion. Postoperatively, a nasogastric tube can be inserted in case of ≥ two episodes of vomiting of an estimated volume > 200 ml. Any other prescription or change in the treatment plan will be instated and documented at the treating physician’s discretion. The patient will be discharged by the treating physician when the patient is mobilised without the need for aid, has adequate pain control and can eat and drink sufficiently. Also, unblinding is permissible at the attending physician’s discretion if examination of the wound is required for example in case of return to the operating room. All patients are planned to be unblinded at discharge unless unblinding has occurred prior. When unblinding, a report form is completed. The form includes the date and reason for unblinding the participant. The attending physician, the nurse and the participant are asked to answer their believed method of surgery: ORC, iRARC, or “do not know” and give a reason for their answer before undressing the wound.

Participants are not planned for any additional follow-up outside of the standard. No concomitant care is prohibited during the trial. Therefore, we expect non-retention in the trial to be low.

### Outcomes

#### Primary outcome

The success of blinding will be determined by (1) the number and proportion of participants with unplanned unblinding before discharge in the two treatment arms and (2) the number of participants, attending doctors, and nurses guessing the correct method of operation at unblinding beyond the level of chance. A previous study from our institution has found a reoperation rate of 22% during the first 90 days after RC with the majority being reoperated during their index hospitalisation [20]. As a reoperation necessitates unblinding, a proportion of < 25% of participants with unplanned unblinding is considered succesfull.

#### Secondary outcomes

There are 12 secondary outcomes as follows:LOSDays alive and out of hospital (DAOH)Conversion (from iRARC to ORC) rateIn-hospital complication rate30-day complication rate90-day complication rateReadmission rateQuality of life (EORTC QLQ-C30 and EORTC QLQ-BLM30)Blood loss (estimated and hidden)PainModerate/severe complications in the PACU (DASAIM discharge criteria)Delirium (3-Minute Diagnostic Interview for Delirium Using the Confusion Assessment Method (3D-CAM)

#### Length of stay (LOS) and days-alive-and-out-of-hospital (DAOH)

The difference in LOS and DAOH between the two treatment arms. Both LOS and DAOH are surrogate markers for recovery after surgery. LOS is calculated as the number of days from the day of operation (POD 0) until the day of discharge and is a commonly reported outcome measure of recovery within ERAS programmes [21]. LOS is affected by local conditions as the perioperative care, discharge criteria, and the post-discharge social care setup. Also, readmissions after RC are frequent and not captured by LOS. On the contrary, DAOH is calculated as days alive and not admitted to hospital from day of operation (POD 0) to 90 days postoperatively. To calculate DAOH, the number of readmissions and the number of days readmitted will be collected.

#### Complication rate

Complications are graded using the Clavien-Dindo system and types of complications are categorised [22]. We will compare complication rates between the two treatment arms. The complication rate will be calculated as the proportion of participants who develop a complication during hospitalisation or within 30 or 90 days. A complication is defined as any deviation from the standard protocol. An unscheduled outpatient visit will be calculated as at least a grade I complication. In-hospital, 30- and 90-day complication rates are chosen as they are frequently used when reporting short-term morbidity after RC.

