### Interventions and blinding

Participants will be randomised 1:1 to receive either ORC or iRARC. All participants are treated in an ERAS setup (Table 1). Upon randomisation, only the operating surgeons, the assistant surgeon, the operating room, and anaesthesiological staff will be informed of the assigned allocation, and none of them are involved in the postoperative care. The treatment allocation is concealed from the patients, treating physicians, staff at the PACU and the urological ward, and the outcome assessor until discharge.

**Table 1 Tab1:** List of components in Rigshospitalet’s Enhanced Recovery After Surgery protocol for radical cystectomy

Preoperatively	
- Pre-operative education and counselling: surgical details, hospital stay, and discharge criteria	
- Stoma education with a specialised stoma nurse	
- Preoperative medical evaluation and optimization	
- Advice and support for smoking cessation and reduction of alcohol intake	
- Instruction on postoperative mobilisation and physiotherapy	
- Anesthesiologic assessment	
Day before operation	
- Admission to hospital	
- Normal diet with no restrictions	
- Rectal enema the night before surgery; omission of mechanical bowel preparation	
- Pharmacological thrombosis prophylaxis with LMWH (Tinzaparin 4500 IE)	
POD 0: preoperatively	
- Preoperative fasting: normal diet until 6 h and clear fluids until 2 h before anaesthesia	
- Preoperative pain medication: Gabapentin 600 mg + Paracetamol 1 g.	
- No long-acting sedatives	
- Elastic compression stockings for thrombosis prophylaxis	
POD 0: intraoperatively	
- Antimicrobial prophylaxis: i.v. Cefuroxime 3 g intraoperative and skin preparation	
- Anaesthesia is similar between groups, including orotracheal intubation, total intravenous anaesthesia (Cisatracurium, Remifentanil, and Propofol), Ondansetron 4mg, Dexamethasone 24 mg, Tranexamic acid 1000mg, i.v. oxycodone and regional anaesthesia using rectus sheath blocks (2 mg bupivacaine/kg body weight) at the end of surgery without epidural	
- Central venous catheter (vena jugularis interna dexter)	
- Radial arterial line	
- Prevention of intraoperative hypothermia (Bair Hugger)	
- Nasogastric tube inserted and removed before extubating	
- No resection site drainage	
- Bilateral ureteric stents	
POD 0: postoperatively	
- Admission to the postoperative care unit until POD1	
- Chewing gum (throughout admission to hospital)	
- Antibiotics Cefuroxime 1500 mg x 3 i.v. (continued for 3 days)	

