- Thrombosis prophylaxis: LMWH (continuing 4 weeks postoperatively) and compression stockings (until discharge)	
- Analgesics: Gabapentin 600mg+300 mg (continued for 3 days) + Paracetamol 1 g x 4 (continued throughout admission), *short-acting* opioids (oxycodone or morphine) if necessary	
- Laxatives: macrogol 1 sachet x 2	
- Antiemetics: Metoclopramide 10 mg if needed	
- Mobilisation: sitting and standing in the evening	
- Oral nutrition: maximum 1 L I fluid, no solids	
- Fluid strategy: Goal directed fluid therapy by stroke volume optimization	
- Continuous Positive Airway Pressure (CPAP) every second hour except during nighttime (24–06)	
POD 1	
- Admission to the urological ward	
- Medication and thrombosis prophylaxis: see “POD 0 postoperatively”	
- Oral nutrition: solids as tolerated, maximum of 1 L of fluids	
- Mobilisation: sitting as much as possible in a chair, walk minimum 2 x 60 m with a walking frame with wheels	
- Self-administration of thromboprophylaxis injections and individually adapted level of self-sufficient care for ileal conduit throughout their hospital stay in preparation for discharge	
POD 2	
- Medication and thrombosis prophylaxis: see “POD 0 postoperatively”	
- Oral nutrition: no restrictions	
- Mobilisation: out of bed minimum 2 x 3 h, walk minimum 3 x 60 m	
POD 3	
- Medication: see “POD 0 postoperatively”	
- Oral nutrition: no restrictions	
- Mobilisation: out of bed minimum 8 h, walk minimum 3 x 60 m	
- Discharge if fulfilling discharge criteria	
POD 4 and until discharge	
- Medication: Paracetamol 1 g x 4, macrogol 1 sachet x 2. Metoclopramide and short-lasting opioids if needed.	
- Mobilisation: as POD 3	
Discharge criteria	
- Adequate pain control	
- Independently mobilised	
- Instructed in stoma care, and establishment of post-discharge specialised assistance if needed - No sign of ileus	
- Adequate oral intake	
Discharge	
- Unblinding	
- Provision of support network including district nurse and urology nurse	
- Information on signs and symptoms of complications. Informed to contact the department by telephone at all hours in case of signs of complications for consultation with a urological nurse or doctor on further actions.	
Post discharge	
- Removal of ureteric stents and skin suture on POD 10 with creatinine blood sample on POD 11	
- Contact with a nurse by telephone the first Thursday after discharge	

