Before the start of the protocol, all study personnel have been trained in the protocol setup. The procedure will be booked as an open procedure in the electronic operating booking system and scheduled from 9 a.m. to 2 p.m. regardless of the method of surgery used. At admission, a note stating that the patient is included in this project will be placed on the patient’s bed. All personnel, including porters, are instructed not to discuss the method of the surgical procedure with the patient. All patients are operated in the same operating theatre in which the da Vinci® Surgical System robot is placed. Anaesthesia is similar between groups, including orotracheal intubation, total intravenous anaesthesia (cisatracurium, remifentanil, and propofol), i.v., oxycodone and regional anaesthesia using rectus sheath blocks (2 mg bupivacaine/kg body weight) at the end of surgery without an epidural. No pre-planning of the operating theatre is performed before the patients are sedated. Both ORC and iRARC follow the same surgical template which includes pelvic lymph node dissection and urinary diversion with an ileal conduit. The extent of the lymphadenectomy will be with the following boundaries: cranially the aortic bifurcation, laterally the genitofemoral nerves, anteriorly the pubic symphysis and the inguinal ligaments, inferiorly the pelvic floor, and posteriorly including the pre-sacral lymph nodes. All wounds are closed using non-absorbable suture. Both primary surgeons and the assisting surgeon will stay in the operating room or an adjacent room to the operating theatre throughout the entire pre-booked time period. The window in the door to the operating room will be covered by a curtain. The operating room is not located adjacent to the other urological operating rooms and no surgeon from the urological ward will pass the used operating room. A temporary standard operation report is used for all patients. In this description, important information on pathology findings and intraoperative complications are included in a manner that does not reveal the surgical method, but data on estimated blood loss (EBL) and time of surgery are left out. A detailed and final operation report will be written by the primary surgeon and kept electronically at the primary surgeon’s password-protected personal drive. The final operation report will be placed in the electronic health record (EHR) at discharge. A printed version of the temporary standard operation report will be kept in a sealed envelope in a hidden place at the Department of Urology. If necessary, this can be obtained at any time by contact with the principal investigator (PI). The abdomen will be dressed to cover wounds from both an ORC and an iRARC (Fig. 1). An adhesive non-transparent, highly absorbent dressing (i.e., Allevyn®) will be used to cover possible exuding from the wounds. The dressing is applied by the surgical team in the operating theatre. Patients are admitted to the PACU after the surgery, where similar postoperative care is performed for both groups, including goal-directed fluid therapy by cardiac output monitoring. On POD1 they are transferred to the urological ward unless the DASAIM discharge criteria are not fulfilled [19]. The dressing will not be changed unless required (because of strike-through or lack of adherence). In this case, a nurse from the neighbouring urological ward, who is not otherwise involved in the care, will be summoned. When changing the dressing, a pillow will be placed on the chest of the patient to maintain blinding of the patient. In the nurses’ office at the ward, a laminated short guide on what to do in specific situations is placed on the wall. Also, alongside this is placed a template of an abdomen with instructions on how to change and place the dressings to keep it standardised. If at any time it is assessed necessary to inspect the wound (e.g., suspicion of wound dehiscence), this can be done and documented. The dressing will be inspected for strike-through of excess exudate by a person not otherwise involved in the care of the patient at least once a day before rounds and changed if needed. [name] will ensure that participants follow the ERAS protocol. Reasons for not complying with the protocol will be registered. Patients are planned to be discharged on POD3 if fulfilling discharge criteria as outlined in Table 1.

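### The complication definition has no minimum grade and, as written, takes in missed ERAS targets, so it can inflate and blur the three any-grade complication rates

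*Protocol article*

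**What the plan says.** Under Outcomes, Complication rate, the protocol article first says "Complications are graded using the Clavien-Dindo system and types of complications are categorised". It then fixes the outcome: "The complication rate will be calculated as the proportion of participants who develop a complication during hospitalisation or within 30 or 90 days". The definition follows: "A complication is defined as any deviation from the standard protocol". One borderline case is settled: "An unscheduled outpatient visit will be calculated as at least a grade I complication". No minimum grade applies to the rate, and no type of deviation is excluded.

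Under Interventions and blinding, the term protocol, when used of perioperative care, means the hospital's ERAS programme. Table 1 lists its components for both arms. Some are fixed daily targets, for example on POD 2: "Mobilisation: out of bed minimum 2 x 3 h, walk minimum 3 x 60 m". The same section says "Reasons for not complying with the protocol will be registered", but not that such non-compliance is kept out of the complication count.

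**The concern.** A complication rate should measure morbidity. A definition that rests on departure from a care programme also picks up adherence: a patient who feels well but walks twice instead of three times on POD 2 has departed from Table 1. Because the outcome is a yes/no per participant, one such departure is enough. A miss during the stay also counts in all three windows, so it raises the in-hospital, 30-day and 90-day rates together.

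At stake are three of the 12 outcomes listed under Secondary outcomes. The article chose these rates because they are common measures of short-term morbidity after cystectomy, and it plans to publish the 30- and 90-day rates. If adherence is mixed in, the any-grade rates are harder to compare with other reports and harder to use in planning a later trial. Two assessors who both follow the text could also classify the same patient differently.

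**Working it through.** The article states no expected complication rate and no ERAS compliance rate, so there is no figure to reproduce. Its only morbidity figure, a 22% reoperation rate within 90 days (Primary outcome), is not a complication rate and does not settle the size. What follows is an illustration.

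**Inputs from Table 1, POD 0 to POD 3**
- Mobilisation items: one on POD 0 (sitting and standing, counted once), and two each on POD 1, POD 2 and POD 3. That is 1 + 2 + 2 + 2 = 7.
- Adding the CPAP schedule gives 8. Adding the 1 L fluid limits on POD 0 and POD 1 gives 10.
- Two of the seven mobilisation items carry no number (POD 0, and sitting on POD 1). Counting numeric items only gives 5 + 1 + 2 = 8.

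**Assumptions, not in the document:** a miss rate q per item of 2% to 30%, and independence between items.

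**Step 1. Participants flagged by missed targets alone:** m = 1 − (1 − q)^k for k items. For example, q = 10% and k = 8 give 1 − 0.90^8 = 0.57.

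| q | k = 7 | k = 8 | k = 10 |
|---|---|---|---|
| 2% | 13% | 15% | 18% |
| 5% | 30% | 34% | 40% |
| 10% | 52% | 57% | 65% |
| 20% | 79% | 83% | 89% |
| 30% | 92% | 94% | 97% |

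To flag 95% needs q = 1 − 0.05^(1/k), which is about 35%, 31% and 26% for k = 7, 8 and 10.

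**Step 2. Effect on the contrast.** Assume medical complication rates of 60% and 40%, the same m in both arms, and misses independent of complications. The observed rate is p′ = 1 − (1 − p)(1 − m), so the difference becomes 20 × (1 − m) points. With k = 8:
- q = 5%, m = 0.34: 73.6% vs 60.4%, 13.2 points.
- q = 10%, m = 0.57: 82.8% vs 74.2%, 8.6 points.
- q = 20%, m = 0.83: 93.2% vs 89.8%, 3.4 points.

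**Step 3. Relaxing the assumptions.**
- If every miss falls in a patient who already has a complication, nothing is added and 60% vs 40% stands.
- If miss rates differ by arm, the direction is open. With m = 0.34 in the 60% arm and 0.57 in the 40% arm, the rates are 73.6% vs 74.2% and the contrast is gone. With the values exchanged, they are 82.8% vs 60.4%, or 22.4 points, and the contrast grows.
- Unequal rates are conceivable: the Discussion itself says that knowing the procedure might affect the advice given on mobilisation.

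**The case against.** The strongest reply is that the section, read as a whole, means medical events. It opens with Clavien-Dindo grading, ends on short-term morbidity, and settles its one borderline case by giving it a grade. It never says that the standard protocol means each line of Table 1, and many lines there are flexible: solids as tolerated, no restriction on nutrition from POD 2, opioids and antiemetics only if needed. Table 2 lists Clavien-Dindo assessment, adverse events and reasons for not being discharged in separate rows, so the data may well be kept apart in practice.

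Much of this stands. Medical events were probably intended, and the exposure is confined mainly to walking, time out of bed, CPAP and early fluids. It does not remove the problem, because the definition is explicit, nothing restricts it to adverse events, and the one clarification given widens the count. This is a rule stated too broadly, not a detail left to the analysis plan.

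A reader might go further and infer that the three rates are driven towards 100% in both arms, mostly reflect adherence and become useless. The document does not support that. It gives no compliance rate, near-saturation needs misses on roughly a quarter to a third of items, and the arithmetic rests on independence and equal miss rates by arm. Patients with ileus or infection are plausibly the ones who cannot walk or eat, so misses may add few new cases.

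**Conclusion.** The concern holds for the any-grade rates. As written, the definition counts ERAS non-compliance as morbidity, and it can inflate the in-hospital, 30-day and 90-day rates and blur the contrast between arms. The size cannot be determined from the document: the range of about 13% to 97% flagged by missed targets alone depends on the assumed miss rate and on independence, and clustering would reduce the effect.

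The reach is limited. I assume that a missed target needing no treatment would be placed at the lowest grade if it were graded at all. Rates restricted to higher grades, such as the grade II to V outcome of one trial described in the Discussion, are then largely unaffected. The primary blinding outcome does not use the definition, and no sample size or success threshold rests on it. This is worth correcting in a descriptive secondary outcome, but it does not threaten the study's main purpose.

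**What to change.** Reconcile the definition with the Clavien-Dindo grading and with the registration of non-compliance under Interventions and blinding:
- Define a complication as an adverse deviation from the normal postoperative course that meets a Clavien-Dindo grade. The existing rule on unscheduled outpatient visits can stay.
- State that ERAS non-compliance is not in itself a complication, and analyse it as its own variable from the reasons already registered.
- Report each rate by highest grade, including grade III or above, next to the any-grade rate.

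The cost is one or two sentences. Table 2 already schedules the Clavien-Dindo and adverse-event assessments, so no new data are needed. With 47 of 50 participants enrolled at the time of writing (Trial status), the change affects classification only. It should be made and dated before complication rates are compared by arm, and entries already recorded as grade I or left ungraded should be checked against the new wording.

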#### Quality of life (QoL)

To assess QoL participants will complete the validated EORTC QLQ-C30 and EORTC QLQ-BLM30 at baseline and 90-days postoperatively. EORTC QLQ-C30 has well-established reliability and validity and is frequently used in clinical trials of RC. EORTC QLQ-C30 is however not bladder specific. Therefore, QLQ-BLM30 will be used as an addition. This questionnaire has been used in several publications before but is not validated. Since most studies use the EORTC QLQ-C30 and QLQ-BLM30 comparative integration of the results in the existing literature will be easy. Patient-reported outcomes are reported according to standards recommended by the 2010 Consolidated Standards of Reporting Trials (CONSORT) PRO extension [23].

#### Blood loss

Formulas exist for estimating blood loss using blood samples (haemoglobin), number of transfusions, and estimated blood volume [24]. We will collect both EBL as well as measures for estimating blood loss by a formula.

#### Pain

The difference in daily visual analogue scale and consumed daily and the total amount of opioids will be compared between the two treatment arms.

#### Post-anaesthesia care unit complications

The difference in rate of moderate/severe complications in the PACU and time from surgery to development of a moderate/severe complication in the PACU. A moderate/severe complication is defined as a score of > 1 according to the discharge criteria scoring system recommended by DASAIM [19].

#### Delirium

The occurrence of acute postoperative delirium is assessed by the Danish version of the 3D-CAM on POD 0 and POD 1 before discharge to the urological ward.

A schedule of enrolment, intervention, and assessments is depicted in Table 2.

**Table 2 Tab2:** Participant timeline

	Preoperative		Perioperatively (RC)	Postoperatively		
Assessment	Outpatient visit	Baseline	POD 0	POD 0 - discharge	Discharge – POD 90	POD 90
Enrolment						
Eligibility screen	x					
Informed consent	x					
Allocation		x				
Medical history, demographic data		x				
Physical examination incl. blood pressure, weight		x		x		
MMSE		x				
Questionnaires						
EORTC QLQ-C30		x				x
EORTC QLQ-BLM30		x				x
Paraclinical examinations:						
Blood samples		x	x	x		
Intraoperative data					x	
3D-CAM				x^*^		
Daily morphine use				x		
Reason(s) for not being discharged				x		
Clavien-Dindo assessment				x	x	x
Adverse events			x	x	x	x
LOS and DAOH						x
Blood loss					x	

*POD* postoperative day, *MMSE* Mini-Mental State Examination, *EORTC* European Organisation for Research and Treatment of Cancer, *3D-CAM* 3-Minute Diagnostic Interview for Delirium Using the Confusion Assessment Method, *LOS* length of stay, *DAOH* days alive and out of hospital

^*^Only assessed POD 0 and POD 1

